### Outcomes

**
*Primary outcome measure.*
** The primary outcome measure of this study is the participant’s time to lesion resolution without any serious complications. Lesion resolution is the first day on which all lesions are resorbed, scabbed or desquamated and mucosal ulcers healed. Lesion resolution is assessed until a maximum of 14 days since the date that the diagnostic sample is taken (for participants who do not receive mpox-specific antiviral treatment) or the day of treatment initiation (for participants who receive mpox-specific antiviral treatment).

**
*Secondary outcomes.*
** Secondary outcome measures evaluate clinical and virologic outcomes. Clinical outcomes are assessed on the basis of:

1. Clinical status on day 14 and day 28 according to a four-point ordinal scale assessed by a physician or a study nurse. The ordinal scale is a) all lesions are resolved and no serious complications, b) active lesions and no serious complications, c) serious complication and/or hospitalization due to mpox, or d) death.2. Evidence of recrudescence or relapse at day 60 and day 180.

*Note:* A "serious complication" is any complication associated with a Serious Advent Event (SAE) that is life-threatening, results in hospitalisation, prolongation of existing hospitalisation, disability, incapacity, or a congenital anomaly; or any other complication that is considered medically significant.

Virologic outcomes in Tier 1 are assessed on the basis of:

1. Change from baseline in mpox virus DNA levels in throat swabs on days 4, 8, 14 and 28.2. Change from baseline in mpox virus DNA levels in blood on days 4, 8, 14 and 28.3. Presence of mpox virus DNA in lesion swabs on days 4, 8, 14 and 28.

The study also assesses the number and type of SAEs, Suspected Adverse Reactions (SARS) and Suspected Unexpected Serious Adverse Reactions (SUSARs) within 28 days of enrolment.

Pregnancy outcomes defined as the final known health status of the mother and child are evaluated in any participants who are pregnant during the course of the study.

**
*Exploratory outcomes in Tier 2 and Tier 3.*
** Further virologic and immunological outcomes are also evaluated in France under this protocol to learn more about viral transmission, humoral and cellular immune responses. The outcome measures are as follows:

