### Data collection methods

All data are recorded by the clinical and study teams directly on the REDCap (version 13.1.30)
^
9
^ electronic Case Report Form (eCRF) for each timepoint as defined in
Table 1.

**
*Demographics and medical history.*
** Data relating to the participant’s demographics and medical history are collected at baseline. Demographic includes sex at birth and ethnic group. Medical history includes data on comorbidities, results of pregnancy and HIV tests, data on signs and symptoms experienced by the participant between the collection of mpox diagnostic sample and the point of consent, and details of potential AEs and SAEs occurring between the collection of mpox diagnostic sample and the point of consent.

**
*Medical assessments.*
** Medical assessments are undertaken at baseline, and D14, 28, 60, and 180. These assessments can be conducted in person,
*via* video link or telephone. The data collected include the participant’s signs and symptoms, any treatment they may be receiving for mpox, AEs and SAEs details.

**
*Biologic sampling.*
** Baseline samples are the participant’s diagnostic samples that may have been collected under routine care before the participant signed the consent form. Blood* (~0.5ml to 20ml depending on local collection procedures), two lesion swabs and one throat swab are collected at D4*, 8*, 14, 21* and 28 where feasible to do so and permitted under local and national regulations–the asterisk (*) denotes procedures only for hospitalised subject; day 21 and 28 sampling only if day 14 sample is still positive.

Where local capacity limits sample collection, sites should prioritise the collection of D14 and 28 samples. All samples are tested by PCR only conducted in local laboratories in each participating country.

In Tier 2 in France, in addition to the sampling covered in Tier 1, additional samples of mucosa, saliva, anus, urine, semen or vaginal secretions, and blood are collected at baseline, D8, D14, D28, D60 (in case of oral, genital or anal lesion) and D180 (only if sample is positive at D60).

In Tier 3 in France, in addition to the sampling covered in Tier 1 and 2, additional samples of blood are collected at D28, D60 and D180.

Samples in Tier 2 and 3 are tested as in
Table 2.

**Table 2. T2:** Tests by sample type.

TIER	Test	Sample							
		Lesion	Throat	Mucosal lesion	Saliva	Anus	Blood	Urine	Semen or vagina secretion
1	PCR	X	X				X		
1&2	Bacterial STIs detection		X			X	X	X	

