Regarding virologic endpoints, the analysis will present the medians and interquartile ranges of mpox virus levels, measured in Cycle threshold (Ct) values, at different time points including baseline, and on days 4, 8, 14, and 28. These measurements will be used to assess viral clearance, categorized as a binary variable, in blood, skin lesions, and throat. The frequency of viral clearance will be reported based on the day of follow-up and treatment status groups.

Additionally, change in mpox virus DNA levels in throat and blood swabs will be compared to baseline on days 4, 8, 14, and 28 and will compared between treatment status using linear regressions at each timepoint.

Logistic regressions will model the presence of mpox virus DNA in lesion swabs at each timepoint.

Regarding safety endpoints, the number and type of SAEs, SARS and SUSARs within 28 days of enrolment will be described.

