### Statistical method

**
*Analysis population.*
** All eligible participants will be included in the final analysis,
*i.e.*, the final analysis set will be the overall population of enrolled participants (prospective and retrospective, with positive mpox PCR).

**
*Method to account for missing, unused or invalid data.*
** The number, timing and pattern for missing values will be detailed for each outcome measure. For missing primary time-to-event outcome:

The patients who are lost to follow-up or withdrew from the trial and who did not experience the event will be censored at their lost to follow-up or withdrawal datePatients who died before experiencing the event will be censored at day 14If the patient is hospitalized, the event will be censored at hospital discharge day, whereas if the patient is an outpatient, the event will be censored at the last available date in the medical assessment formsIf the outcome is still missing, it will be searched in the Patient Self-Assessment Surveys (PSA)

For the four-point clinical scales at day 14 and day 28, missing data will be imputed by using the last observation carried forward (LOCF) method for “Death” and “All lesions are completely resolved and no serious complications” modalities. Missing outcomes will be searched as done for the primary endpoint.

Endpoints still missing after these recovery steps will remain missing in the analyses.

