Beyond the operational aspects, starting clinical research for under-researched diseases like mpox is often slowed down by the lack of established methodologies for defining outcomes and endpoints to assess the disease and the treatment effect. MOSAIC benefitted from the tecovirimat Expanded Access Programme (EAP) protocol underway in the Central African Republic (CAR), which could be quickly adapted to the clade IIb
^
6
^, and from experience with
clinical characterisation protocols. Outcomes have also further been harmonised across several other studies and trials currently running or planned on mpox: randomised clinical trials of Tecovirimat (
Platinum in the UK (ISRCTN17461766) and in Canada (NCT05534165), Unity in Switzerland, Brazil and Argentina (NCT05597735), Stomp (NCT05534984), EPOXI in Europe, PALM007 in Democratic Republic of Congo (NCT05559099), MOSA in Africa), EAPs (the US Army EAP (NCT02080767) and the Tecovirimat for mpox in Central African Republic (ISRCTN43307947)), the WHO Monitored Emergency Use of Unregistered and Investigational Interventions (MEURI) and observational studies (the
Clinical Characterisation Protocol in UK and Netpox in Brazil (NCT05784038)). So that now hopefully consistent, comparable evidence will be generated, although some methodological questions are still unresolved
^
11
^. At the same time, uncertainties persist about outcomes and study endpoints, both clinical and virologic
^
11
^. For instance, current studies, including MOSAIC, tend define lesion resolution as “For skin lesions, typically this means the lesion has scabbed, desquamated and new layer of skin has been formed. For mucosal lesions, the phase of scabbing and desquamation is absent, and healing with new layer of skin ensues.” (UNITY trial) or “skin lesions are scabbed, desquamated or healed, and visible mucosal lesions are healed” (STOMP trial). However, there appear to be substantial inter-observer differences in lesion classification
^
12
^, and we know that the MPXV persists in scabs in both clade I and II cases
^
13
^. It will therefore be important for future studies to more consistently standardise definitions and lesion assessment.

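### At D14 and D28, lesion DNA presence and clearance are defined only on swabs, so, read literally, participants with no lesion or scab left drop out of any comparison by treatment status

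*Protocol article*

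**What the plan says.** All references are to the protocol article.

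- **Outcomes, Secondary outcomes.** The third Tier 1 virologic outcome is "Presence of mpox virus DNA in lesion swabs on days 4, 8, 14 and 28".
- **Statistical method, virologic endpoints.** "Logistic regressions will model the presence of mpox virus DNA in lesion swabs at each timepoint". Ct values are also turned into a yes/no clearance variable for blood, skin lesions and throat, and "The frequency of viral clearance will be reported based on the day of follow-up and treatment status groups".
- **Statistical method, Analysis population.** "All eligible participants will be included in the final analysis".
- **Statistical method, missing data.** Recovery steps are given for the time-to-event outcome and the four-point clinical scale. On that scale, death and full resolution are carried forward. Then: "Endpoints still missing after these recovery steps will remain missing in the analyses".
- **Outcomes, Primary outcome measure.** "Lesion resolution is the first day on which all lesions are resorbed, scabbed or desquamated and mucosal ulcers healed".
- **Discussion.** On scabs: "we know that the MPXV persists in scabs in both clade I and II cases".
- **Data collection methods.** D4 and D8 carry an asterisk, and "the asterisk (*) denotes procedures only for hospitalised subject". D28 sampling is tied there to a D14 sample that is still positive. Table 1 lists D28 as a priority timepoint without that condition.

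No section says whether a participant examined and found to have nothing left to swab counts as negative, cleared, missing or not applicable.

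**The concern.** Blood and throat can be sampled after recovery. A lesion can be swabbed only while a lesion or scab remains. Under the literal text, someone whose skin has fully healed has no lesion swab and therefore no endpoint, and the general rule leaves it missing. The denominator at each visit then depends on a post-baseline state that an antiviral may change. Adjusting for baseline confounders does not by itself bring back the people who left.

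Two things are at stake at D14 and D28:

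- The lesion clearance frequency describes only people who still have something to swab, so clearance in the cohort is understated. That matters in a study whose analysis is mainly descriptive.
- Any contrast by treatment status can hide a benefit, or reverse it, because those who healed fastest no longer count.

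**Working it through.** **No figure to reproduce.** The article gives no healing rate, positivity rate or sample-size calculation for this endpoint. Every rate below is an assumption that shows the mechanism.

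**Group sizes.** The Discussion reports 601 enrolled, with 55 on tecovirimat, 7 on cidofovir and 2 on both. If these counts are exclusive, 55 + 7 + 2 = 64 are treated and 601 − 64 = 537 untreated. If the 2 are contained in the other counts, 60 are treated and 541 untreated. The first split is used.

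**Formulas.** Let *h* be the proportion resolved, *p* the positivity of an unresolved lesion, and *s* the share of resolved participants who still have a scab to swab, with scab positivity assumed to be *p*/2.

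- Proportion swabbed: (1 − h) + hs
- Positive over all participants, nothing left counted as no lesion DNA: (1 − h)p + hs·p/2
- Positive among those swabbed: the second quantity divided by the first

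**One assumed D14 scenario:** h = 60% untreated and 75% treated, p = 70% in both groups.

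| Resolved participants with a scab to swab | Swabbed, untreated / treated | Positive among swabbed | OR | Positive over all | OR |
|---|---|---|---|---|---|
| None (s = 0) | 215 / 16 | 70.0% / 70.0% | 1.00 | 28.0% / 17.5% | 0.55 |
| Half (s = 0.5) | 376 / 40 | 55.0% / 49.0% | 0.79 | 38.5% / 30.6% | 0.71 |
| All (s = 1) | 537 / 64 | 49.0% / 43.8% | 0.81 | 49.0% / 43.8% | 0.81 |

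First row, worked: 0.40 × 0.70 = 0.28 and 0.25 × 0.70 = 0.175; OR = (0.175/0.825)/(0.28/0.72) = 0.55.

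**Range with s = 0.** With resolution (untreated/treated) from 10/20% to 80/90% and *p* from 50% to 90%, the swabbed-only OR stays at 1.00. The all-participant OR runs from 0.81 (10/20%, p = 50%) to 0.45 (80/90%, p = 90%). The value 1.00 follows by construction from equal *p* in both groups.

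**When severity drives both healing and positivity.** A simulation of 2,000,000 subjects assumed a median healing time of 13 days untreated, shortened by 20% or 30% with treatment. Severe cases healed later and were more often positive. Treatment had no effect on DNA beyond healing, and no scabs were swabbed after healing. Each cell gives the 20% case, then the 30% case.

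| Day | Lesion still present, untreated | Lesion still present, treated | Swabbed-only OR | All-participant OR |
|---|---|---|---|---|
| D4 | 99% | 98%, 96% | 1.03, 1.08 | 0.96, 0.93 |
| D8 | 85% | 71%, 61% | 1.20, 1.36 | 0.72, 0.55 |
| D14 | 44% | 26%, 18% | 1.32, 1.55 | 0.55, 0.36 |
| D28 | 5% | 2%, 1% | 1.37, 1.79 | 0.37, 0.19 |

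The simulation assumes swabbing of everyone with a lesion, as if Table 1 alone governed. Under Data collection methods, D4 and D8 samples come from hospitalised participants only and D28 samples follow a positive D14 sample, so the D4, D8 and D28 rows would not describe the sampled group.

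**The case against.** **The analysis plan may settle it.** The article leaves derivations to a separate statistical analysis plan, and coding *examined, no lesion* as cleared is compatible with its text. The missing-data recovery steps were written for other outcomes and do not call a healed lesion a missing value. This stands in part: the dropout is a literal reading, not a stated rule. But the endpoint is already worded on swabs and the closing missing-data rule is general. Healing is protected by carry-forward only on the ordinal scale.

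**A reader might infer that the comparison is made among slow healers only, or that the primary outcome itself selects the denominator.** The documents do not support either. Resolution includes scabbed lesions, which can still be swabbed and may carry virus, so resolved and nothing left to swab are different states. If every resolved participant kept a scab, nobody would leave. Under the assumed healing times nearly everyone still has a lesion at D4 and most do at D8. At those visits the restriction to hospitalised participants is the stronger selection.

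**The treatment contrast is indirect.** The lesion regression sentence names no treatment term. The contrast comes from reporting clearance by treatment status and from the general causal-inference plan. This is correct, and it limits the point to those uses.

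**Positivity among remaining lesions is a legitimate quantity, and a composite mixes healing into a virologic endpoint.** Also correct. In the D14 scenario with no scabs swabbed, the whole all-participant difference comes from healing. Both quantities should therefore be reported, each labelled for what it is.

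**Conclusion.** The point holds for D14 and D28, weakly for D8 and not for D4. As worded, the lesion DNA endpoint, its regression and the clearance frequency rest on swabs. Participants with no lesion or scab left therefore have no value unless a rule is added. A comparison by treatment status is then conditioned on a post-baseline state related to, but not identical with, the primary outcome.

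The size cannot be known from the article. Under the assumed rates the swabbed-only odds ratio is 1.0 or above while the all-participant ratio is about 0.45 to 0.8, and lower in the simulation at the late visits. If half of resolved participants can still be swabbed, the assumed D14 gap narrows to 0.79 against 0.71; if all can, it disappears. The statement that clearance is understated assumes that a fully healed site carries no lesion DNA.

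**What to change.** 1. At each visit, code four states: swab positive; swab negative; examined with no lesion or scab left; lesion present but not swabbed, or not assessed. Only the last is missing.
2. Analyse *DNA-positive lesion present* against *negative swab, or no lesion or scab left*, over all participants assessed at that visit. Use the same coding for skin-lesion clearance.
3. Report the number in each state by day and treatment group.
4. Keep positivity among those swabbed, labelled as conditional and descriptive.
5. Reconcile the sampling restrictions in Data collection methods with Table 1, because they add a separate selection.

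**Cost.** This changes the wording of the endpoint and the analysis. Clinical status is recorded at D14 and D28, and the self-assessment survey captures lesion status. The top level of the four-point scale does not separate scabbed from fully healed, so that distinction must come from recorded signs, notes or the survey. With enrolment closed and some participants recruited retrospectively, it will not always be recoverable, and those cases stay missing.

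**Downside to state openly.** A fully healed site is assumed free of lesion DNA, and the composite partly reflects healing rather than virus alone.

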## Methods

### Objectives

The primary objective of this study is to describe clinical outcomes of participants with laboratory confirmed MPXV, whatever the treatment administered.

Secondary objectives describe the virologic evolution of mpox, and Adverse Events (AEs) and Serious Adverse Events (SAEs) that occur in participants enrolled in the study. In France, additional exploratory objectives aim to evaluate virologic and immunological outcomes to learn more about viral transmission and induced immune responses. Among a subset of participants, exploratory objectives are to determine: i) the distribution of MPXV within the different anatomical sites of the participants, as well as the duration of positivity of the samples at the different sites, and the viral dynamics in patients receiving or not antiviral treatments (including tecovirimat), ii) the viability of the viruses detected by PCR (cell culture), iii) the intra-individual and inter-individual genetic variability, iv) the potential resumption of human immunodeficiency virus (HIV) viral replication in the blood and semen of participants living with HIV and the presence of other sexually transmitted infections, and v) post-mpox acquired humoral and cellular immunity.

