### Harms

**
*Safety reporting.*
** The assessment of safety outcomes—a study objective—requires adverse event reporting, serious adverse event reporting and collection of pregnancy outcomes in both treated and non-treated cohorts.

The study procedures carry minimal risk and therefore AE related to the study procedures are not anticipated.

AE and SAE data are collected in the eCRF from the date that the participant’s diagnostic sample for mpox infection was collected or the date of enrolment (whichever comes first) until D28.

*

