**Definition of Serious Adverse Events (SAE).**
* The Serious Adverse Events (SAE) are defined as any unfavorable medical occurrence that meets one or more of the following criteria:

Results in the participant's death.Poses a life-threatening risk to the participant's well-being.Requires hospitalization, including cases where it extends an ongoing hospital stay.Leads to persistent or significant disability or incapacity.Involves a congenital anomaly or birth defect.

Additionally, other "important medical events" may also be considered serious adverse events if, based on appropriate medical judgment, they have the potential to jeopardize the participant's health and necessitate medical or surgical intervention to prevent any of the outcomes mentioned above.

It is important to note that the term "life-threatening" within the definition of "serious" pertains to events where the participant was at risk of death at the time of the occurrence. It does not refer to events that hypothetically might have caused death if they were more severe.

All SAEs (including a site investigator causality assessment) should be reported by the site to the sponsor within 24 hours of the site becoming aware of the event and their causal relationship to tecovirimat (or other antivirals) are assessed. The Sponsor reviews all SAE reports received and conducts the causality and expectedness assessment of the event. Additional information (including the reason for considering the event both serious and related, and relevant medical and medication history) may be sought from the reporting site. The expectedness assessment considers Section 4.8 of the EMA Summary of Product Characteristics (SmPC) as Reference Safety Information for tecovirimat. Where possible, Section 4.8 of the relevant EMA SmPC is also used to assess the expectedness of the event for any other antiviral used in the study. The Sponsor conducts a causality and expectedness assessment within one business day of receiving the SAE report to determine whether the event is an SAE, SAR or SUSAR. In the event of divergent causality assessments by the site investigator and the Sponsor, both assessments are recorded and the assessment determining the strongest relationship defines the event as a SAE or SAR.

If there is a reasonable probability that any SAE is caused by tecovirimat or any other antiviral medication, it is considered a Suspected Serious Adverse Reaction (SSAR).

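### The secondary objective covers all adverse events, but no listed safety outcome or analysis covers non-serious adverse events as a class

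*Protocol article*

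**What the plan says.** **Objective.** In the Objectives section, one secondary objective is to describe "Adverse Events (AEs) and Serious Adverse Events (SAEs) that occur in participants enrolled in the study".

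**Collection.** Table 1 (footnote b) and the Data collection methods section have AEs and SAEs recorded at baseline. The later medical assessments record "any treatment they may be receiving for mpox, AEs and SAEs details". The Harms section states that "AE and SAE data are collected in the eCRF", up to D28. It also says that assessing safety, which it calls a study objective, "requires adverse event reporting, serious adverse event reporting and collection of pregnancy outcomes in both treated and non-treated cohorts".

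**Outcome.** The Outcomes section gives the safety measure as "the number and type of SAEs, Suspected Adverse Reactions (SARS) and Suspected Unexpected Serious Adverse Reactions (SUSARs", counted over 28 days from enrolment.

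**Analysis.** The safety sentence of the Statistical method section reads: "the number and type of SAEs, SARS and SUSARs within 28 days of enrolment will be described".

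**Classification.** Under the definition of SAEs in the Harms section, sites report SAEs to the sponsor and "their causal relationship to tecovirimat (or other antivirals) are assessed". The sponsor then uses the SAE report to class the event as SAE, SAR or SUSAR. The same section introduces a further category, SSAR, for SAEs probably caused by an antiviral, and goes on to name SAR and SSAR side by side.

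**The concern.** The objective and the data collection name AEs; the outcome and the analysis do not. If the outcome and analysis are followed as written, part of a stated secondary objective has no result attached to it, although the data will have been collected.

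What is at stake is the description of tolerability and of the non-serious course of illness, in treated and untreated participants alike. The section on early discontinuation lists adverse events that a participant finds intolerable as a reason for withdrawal. Such an event, if not serious, has no clear place in the planned safety results.

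**Working it through.** There is no figure in the plan to reproduce. The check sets the sections side by side.

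| Section | All AEs | SAEs | SARs and SUSARs |
|---|---|---|---|
| Objectives | named | named | not named |
| Table 1 footnote b; Data collection methods | collected | collected | not named |
| Harms, safety reporting | collected to D28; said to be required in both cohorts | collected to D28; said to be required in both cohorts | not named |
| Outcomes | **not named** | named | named |
| Statistical method, safety sentence | **not named** | named | named |

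*Step 1.* The outcome list and the analysis list agree with each other, so the omission is not a slip in one sentence. Both differ from the objective and from what is collected.

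*Step 2.* Could SAR bring non-serious events back in? The document points both ways.
- Broad reading: the Outcomes section spells SAR out without the word serious, and the Harms section names SSAR as a separate category. SAR could then include non-serious suspected reactions.
- Narrow reading: the only process described that assigns SAR starts from an SAE report. On that route a SAR is always serious.

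*Step 3.* What falls outside the listed outcomes on each reading?
- Narrow: all non-serious AEs.
- Broad: all non-serious AEs not suspected to be drug-related. The Harms section treats SARs and SSARs as events linked to treatment. A participant with no antiviral has no drug to suspect, so every non-serious AE in that participant is outside.

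*Step 4.* How many participants does the common part concern? The Discussion reports 601 enrolled, with 55 treated with tecovirimat, 7 with cidofovir and 2 with both.
- If the three counts are separate: 55 + 7 + 2 = 64 treated; 601 − 64 = 537 untreated; 537/601 = 89%.
- If the 2 are already included in the 55 and the 7: 55 + 7 − 2 = 60 treated; 601 − 60 = 541 untreated; 541/601 = 90%.

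Both assume that no other antiviral was used. These are numbers of participants, not of events; the document gives no AE frequency.

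**The case against.** The strongest case against has four parts.

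1. *SAR may already cover the events that matter most.* If SAR meant serious reactions only, a separate SSAR category would be redundant. The text that assigns SAR from SAE reports sits under the definition of SAEs. It does not say that non-serious AEs receive no causality assessment, and full reporting details are in appendices that are not shown. This stands to the extent that non-serious suspected reactions may be counted. It does not reach non-serious AEs not suspected to be drug-related.

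2. *The statistical analysis plan will describe the safety variables.* The article says so, and the layout of AE tables is normal content for that plan. But the article itself fixes an explicit outcome list, and that list does not match its own objective. That is a contradiction within the document, not detail left for later.

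3. *AEs are looked at elsewhere.* The medical monitor periodically reviews a listing of all AEs, and the eCRF records the reason for withdrawal. Both are true, but the first is oversight and the second is a disposition record. Neither is a study outcome or a planned result.

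4. *Data quality.* From January 2023 patients were recruited retrospectively, and the eCRF may be completed from existing medical notes. Non-serious AEs may be under-recorded there. This stands as a limit on how an AE table should be read, not as a reason to omit one.

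A reader might infer that non-serious AEs are never reported. The documents do not support that: SAR as spelled out in the Outcomes section may include non-serious reactions, the medical monitor sees all AEs, and the analysis plan, not shown here, may add a summary.

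**Conclusion.** The concern holds in this form: the secondary objective and the data collection cover AEs and SAEs, while the listed outcome and analysis cover only SAEs, SARs and SUSARs. No listed outcome or analysis covers non-serious AEs as a class. On either reading of SAR, those not suspected to be drug-related are left out, which includes all non-serious AEs in the 537 to 541 participants without an antiviral. Whether non-serious suspected reactions in the 60 to 64 treated participants are counted cannot be settled from the text.

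This rests on reading SAR as a reaction to an antiviral, as the Harms section does, and on the treatment counts in the Discussion. The small treated group limits how precise any AE proportion would be, but no precision calculation bears on a mismatch of wording. It would also be too much to say that half of the safety objective is unanswered: SAEs are themselves AEs, and suspected reactions are listed. The point is a modest one that should be corrected.

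**What to change.** 1. In the Outcomes section and in the safety sentence of the Statistical method section, add the number and proportion of participants with any AE, by type, seriousness and treatment status, from the AE data already in the eCRF to D28.
2. Define SAR and SSAR once, stating whether SAR includes non-serious reactions, and use both terms consistently in the Outcomes, Statistical method and Harms sections.
3. Show the AE results separately for prospective and retrospective enrolment, or state beside the table that non-serious AEs may be under-recorded in retrospectively enrolled participants.

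The cost is one extra descriptive table and some rewording, with no new data. Adding a causality assessment for non-serious AEs is not proposed, because it could require data not now in the eCRF.
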